### Research gaps

A central question is whether tonic and phasic irritability reflect different intensity levels along a single continuum or constitute related but distinct phenotypes.^34^ This study uses ecologically valid, multimodal and multi-informant assessments, as well as EMA, to characterise both dimensions. By integrating cognitive, psychosocial, psychophysiological and autonomic measures, the study aims to clarify within-person dynamics and identify proximal markers of tonic and phasic irritability. This approach will also allow for the examination of their concurrent and longitudinal associations with clinical outcomes, with the goal of laying a foundation for future work improving early identification and intervention targets.

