### The current research project

The overall objective of this research project is to develop a fine-grained, ecologically valid and multimodal characterisation of tonic and phasic irritability in order to better understand the differential role of the two components of irritability in developmental psychopathology. In particular, through ESM assessment, our *first aim* is to validate the tonic—phasic distinction of irritability at the within-person level and to determine the temporal dynamics as well as the natural context of expression of the two components. We hypothesise that the tonic and phasic components of irritability measured with ESM will be strongly and consistently associated with their respective well-established clinical measures, thereby providing new, reliable and complementary measures. We further assume that high levels of tonic irritability will precede phasic irritability (i.e., temper tantrum). Moreover, contextual information (including parenting) about the current psychosocial environment might be differently related to tonic vs phasic irritability.

Our *second aim* is to examine whether distinct cognitive and autonomic correlates of tonic and phasic irritability exist, both at the within-person level and at the between-person level. Related to this aim, we hypothesise that experimental measures of ambulatory cognitive control will be more strongly associated with phasic than tonic irritability. From the ‘in-situ’ assessment, we expect that HRV reactivity will be more specifically related to phasic aspects of irritability (clinical and ESM assessments), whereas HRV recovery (more related to emotion regulation) will be associated with tonic irritability (ESM and well-established clinical assessments). Finally, by means of the autonomic EMA, we expect to identify autonomic dysregulation concurrent with tonic irritability but probably preceding episodes of phasic irritability.

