### Statistical analysis plan

We will assess cross-language measurement invariance (French vs German) for multi-item scales using multi-group confirmatory factor analysis, testing configural, metric and scalar (threshold) invariance based on model fit and Δcomparative fit index (CFI)/Δroot mean square error of approximation (RMSEA). If inter-site differences are detected, the site will be included as a covariate in the statistical models to control for potential confounding.

#### Aim 1

First, we will compute separate standardised composite scores for tonic and phasic irritability at the within- (from the ESM measures) and between-person level (from the interviews and questionnaires). To assess convergent validity, multilevel regression models will then be used to test for associations between the tonic irritability composite score from ESM measures and the tonic irritability composite score from the clinical measures. The same models will be computed for phasic irritability. To test our second hypothesis, we will compute a lagged logistic multilevel regression model where tonic irritability from one ESM sampling will predict the presence of phasic irritability (categorical score) in the next ESM sampling (within-person level). Finally, to investigate the role of the psychosocial context (including parenting), multilevel regression analyses will be used to assess the role of conflict and psychosocial context on tonic/phasic irritability at the within-person level.

#### Aim 2

To test the pathophysiological correlates of tonic and phasic irritability, we will compute a multivariate linear mixed model,^115^ which represents a statistical framework for analysing fixed and random effects on multiple outcomes (i.e., tonic vs phasic irritability).^116^ This approach enables us to compare the effects of the pathophysiological variables on tonic versus phasic irritability, which are two separate but correlated outcomes. The model will hence allow computing effect sizes that will be compared with assessing the common and unique pathophysiological correlates (i.e., ambulatory cognitive control, ‘in-situ’ HRV) of tonic and phasic irritability both at a within- and between-person level. Lagged multilevel regression models will further be used to assess the temporal dynamics of the pathophysiological (e.g., ambulatory HRV, actigraphy and cognitive control) correlates of tonic and phasic irritability at the within-person level.

#### Aim 3

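### The Aim 1 validity step tests only same-component links between children, so one irritability trait would pass it as readily as two

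*Protocol article*

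**What the plan says.** The Research gaps section treats as central the question "whether tonic and phasic irritability reflect different intensity levels along a single continuum or constitute related but distinct phenotypes". In The current research project, the first aim is to "validate the tonic—phasic distinction of irritability at the within-person level", along with describing temporal dynamics and context. The first hypothesis under that aim is that the ESM components "will be strongly and consistently associated with their respective well-established clinical measures".

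Under Aim 1, the Statistical analysis plan forms composites at two levels. The ESM composites are within-person and the clinical ones are "between-person level (from the interviews and questionnaires". The validity models, labelled as convergent, "test for associations between the tonic irritability composite score from ESM measures and the tonic irritability composite score from the clinical measures". For the other component, "The same models will be computed for phasic irritability".

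Aim 1 has two further analyses, both within-person. In a lagged logistic model, "tonic irritability from one ESM sampling will predict the presence of phasic irritability (categorical score) in the next ESM sampling (within-person level". Other models "assess the role of conflict and psychosocial context on tonic/phasic irritability at the within-person level".

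Aim 1 states no cross-component association, no model with both clinical composites and no comparison of one factor with two. The only factor analysis in the plan is for French-German invariance.

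**The concern.** Showing that two components are distinct needs evidence that each relates more strongly to its own criterion than to the other's. The validity step looks only at the own-criterion links. If one trait drives all four scores, those links are positive anyway, so a positive result is expected whether there is one dimension or two.

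The level is also wrong for the aim. A score that is constant within a child can account only for differences between children in ESM irritability, while the aim is worded at the within-person level. At stake is the first aim: data from a unitary trait could be reported as having met it.

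**Working it through.** **Inputs.** From Power analyses: 220 children, 4 prompts a day for 14 days, compliance 82%, dropout 20%, correlation between repeated measures 0.75, expected tonic-phasic correlation 0.60. Assumed here: two-sided 5% level, since none is stated, and the ESM-clinical correlation, for which a range is shown.

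**The plan's own figures.** 4 × 14 = 56 and 3 × 14 = 42, as stated. The stated power (0.99 within and 0.94 between for the concurrent model) cannot be reproduced exactly, because small and medium effects are given no numbers. By Fisher z, a between-person r of 0.24 gives 0.95 at n = 220, and 0.25 gives 0.92 at n = 176. These figures do not bear on the point.

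**Same and cross associations under one trait.** Let clinical and ESM person scores load on a single trait with loadings c and e. The same-component correlation is c × e. If the loadings do not differ by component, the cross-component correlation is also c × e, whatever its size.

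**Chance that each planned test is positive under one trait.** n = 220 × 0.80 = 176. Power = Φ(atanh(r) × √(n − 3) − 1.96), with √173 = 13.15.

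| assumed r | atanh(r) × 13.15 | minus 1.96 | power |
|---|---|---|---|
| 0.2 | 2.67 | 0.71 | 0.76 |
| 0.3 | 4.07 | 2.11 | 0.98 |
| 0.4 | 5.57 | 3.61 | 0.9998 |
| 0.5 | 7.22 | 5.26 | above 0.9999 |

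**Simulation.** 1000 studies per scenario, n = 176, 56 prompts, 82% compliance, intraclass correlation 0.75. Assumed: all loadings 0.8, and one shared within-person state with autocorrelation 0.3 in every scenario. A phasic event was the top 20% of the phasic score. Correlations of person means stood in for the convergent models, and a person-centred linear probability model for the lagged logistic model. The contrast correlates standardised ESM tonic minus phasic with clinical tonic minus phasic.

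| true trait correlation | mean same-component r | mean cross-component r | both convergent tests positive | lagged model positive | contrast positive |
|---|---|---|---|---|---|
| 1.0 (one trait) | 0.64 | 0.64 | 100% | 100% | 2.6% |
| 0.9 | 0.64 | 0.57 | 100% | 100% | 52% |
| 0.75 | 0.64 | 0.48 | 100% | 100% | 98.6% |
| 0.60 | 0.64 | 0.38 | 100% | 100% | 100% |

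The planned convergent tests give the same answer in every row. The lagged model also passes with a single autocorrelated state, because tonic irritability now and phasic irritability at the next prompt both reflect it, and no adjustment for current phasic irritability is stated. The contrast does separate the rows.

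**Caveat on the contrast.** The plan does not say whether its 0.60 is a correlation of true or observed scores. If observed, loadings of 0.8 imply a true correlation of 0.60 / (0.8 × 0.8) = 0.94, and the contrast would succeed less often than the 52% found at 0.9.

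**The case against.** The strongest defence is that the step does what it says. It is labelled convergent validity, its hypothesis concerns agreement with established measures, and the regression tests that. This stands, and it is why the point is limited to what the step can support.

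Three stronger readings are tempting and should not be drawn.

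- A reader might infer that Aim 1 contains only between-child analyses. It does not: the lagged and context models are within-person, and the text expects context to relate differently to the two components. But the lagged model runs in one direction, and no formal tonic-versus-phasic contrast is stated for the context models.
- A reader might infer that the study cannot address the one-or-two question at all. The documents do not rest that question on this step. The Aim 2 multivariate model compares correlates of the two components at both levels, Aim 3 uses mutually residualised scores, and network analyses are exploratory. These give indirect evidence, but they take the two composites as given.
- A reader might infer that the authors would treat a positive convergent result as proof of two phenotypes. The article never says so, and under Scientific relevance it says only that the study might inform the question.

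Nor does the expected correlation of 0.60 carry the argument, since the one-trait case has a true correlation of 1. Finally, an article condenses, and under Dissemination the main analyses are still to be preregistered. That leaves room for the remedy, but the mismatch is between an aim and a test that this article itself states.

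**Conclusion.** The concern holds for the validity step of Aim 1. That step can show that ESM and clinical scores agree between children; it cannot by itself support a within-person distinction. The other Aim 1 models, as stated, do not supply the missing evidence.

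Under one trait, each convergent test is positive with probability 0.76 to above 0.9999 for assumed correlations of 0.2 to 0.5 at n = 176. The equality of same- and cross-component correlations under one trait does not depend on the size of the loadings, only on their not differing by component. The simulated percentages depend on the assumed loadings, autocorrelation and event definition, and the lagged result also on taking the unstated adjustment as absent.

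This should be fixed. It is not critical, because design, sample size and data collection are unaffected and other aims bear on the question indirectly.

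**What to change.** 1. In the Aim 1 validity models, enter clinical tonic and clinical phasic together, for example with ESM tonic and ESM phasic as the two outcomes of the multivariate mixed model already named for Aim 2. Test that the same-component association exceeds the cross-component one. Allow for unequal reliability: under one trait the summed contrast equals (e_tonic − e_phasic) × (c_tonic − c_phasic), which is not zero if the components differ in loading in both sources. This part remains between-person.
2. For the within-person part, compare one- and two-factor two-level models of the ESM irritability items. This needs enough items per component, and the article gives no item counts. Otherwise, formally contrast the within-person context effects on tonic and phasic irritability, and adjust the lagged model for current phasic irritability. That adjustment alone is not decisive: if current phasic irritability is measured with error, a shared state can still act through the tonic score.
3. Failing these, state that this step establishes convergent validity only, and word the first aim to match.

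The cost is a few extra models, and the distinction may not be supported. Data collection runs to the end of 2027 and preregistration is planned, so the models can be fixed before analysis.

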#### Exploratory analyses

Moreover, complementary analyses may be conducted to further understand the clinical value of tonic and phasic irritability. Regarding the cardinal role of irritability in psychopathology, network analyses investigating the interrelationships between irritability, psychopathological symptoms, cognitive control, the psychophysiological and neurobiological measures will be conducted to assess the temporal networks (i.e., within-person, time-series), contemporaneous networks (i.e., within-person, cross-sectional) and between-person networks (i.e., between-person, cross-sectional). Such analyses will provide important information on the temporal and reciprocal relationships among the processes.^119 120^ This may help to understand the centrality of irritability as well as the reciprocal dynamics between tonic and phasic irritability and their interplay with concomitant processes.^119^ In addition, we will conduct fragmentation analyses, which may provide additional information on stability or fluctuations of tonic irritability at the within-person level, compared with standard approaches of variability.^121^ These analyses will help us to determine a range of ‘normal’ variability and thus identify the events outside this range (i.e., between-state transition probabilities). This approach might help to understand the stages where tonic irritability becomes problematic and examine the psychophysiological correlates as well as the future outcomes (e.g., subsequent phasic episode, later conflict). Finally, measures from passive sensing collected in those participants who own a smartphone will be used to relate tonic and phasic irritability as well as its cognitive and autonomic correlates to changes in habits and behaviour (e.g., listening to music, physical activity, sleep, duration or frequency of smartphone usage). As data are obtained passively without interrupting participants and without their own reporting, this data is of highest ecological validity and may pave the way to advance the assessment of irritability in the future. The problem of multiple testing will be considered with appropriate statistical methods and interpretation to avoid type I error (false positives). All analyses will be performed using the R environment for statistical computing V.4.1.0.^122^

The statistical analyses described above were planned when this study was conceptualised. If, during the course of the study, circumstances arise that make this analysis inappropriate or if, in the meantime, better methods of analysis are identified, a different analysis may be performed and will be described in the study report and publication.

#### Power analyses

We approximated the power of the main analyses (i.e., the multilevel regression) by using Monte-Carlo simulation (n=1000 repetitions). Based on pilot studies (unpublished data), we assumed a correlation coefficient of r=0.75 between repeated measures, participant compliance of 82% and an additional dropout of 20%. For the concurrent model, 56 repeated measures for each participant (4× measure a day for 14 days) will be collected for n=220 participants. For the temporal model (or lagged model, predicting next measures), 42 measures (three lagged variables per day for 14 days) will be available for the 220 participants. We expect a correlation between tonic and phasic irritability of r=0.60.^35^ The approximated power of these analyses focuses on the effects of β_n_ (between-person level) and γ_n_ (within-person level) for the repeated measures. These models have a power of 0.99 to detect small effect sizes at the within-person level and a power of 0.94 to detect medium effect sizes at the between-person level. For the temporal model (lagged model), we will achieve a power of 0.91 to detect small effect sizes at the within-person level and a power of 0.82 to detect medium effect sizes at the between-person level.

#### Missing data

Missing data will be minimised through electronic data capture (via REDCap with built-in range checks and completion indicators). Patterns of missingness will be assessed. If data are missing at random, multiple imputation will be applied. If data are missing completely at random, analyses may additionally be performed using expectation-maximisation procedures. Results from analyses on the imputed dataset will be compared with complete-case analyses as part of a sensitivity analysis.

### Patient and public involvement

In this research project, youths were invited to provide feedback in the phase of project development and implementation. For instance, after discussion with a panel of youths, we incorporated gamification elements into the ESM, making the data collection process more interactive and enjoyable and enhancing participant engagement and adherence. As such, we conducted an intensive pilot phase to test the comprehensiveness of the questionnaires and the burden that might be placed on participants by the assessment procedures. A panel of youths was involved to provide feedback to the baseline assessment and the EMA phase. Their valuable feedback was used to refine the questions, ensuring they are clear, concise and easy to understand for all participants. Finally, we intend to involve patient and public involvement partners in the dissemination of the results to the general public.

### Ethics and dissemination

#### Ethics

This research project is conducted in accordance with the protocol, the Declaration of Helsinki, the principles of Good Clinical Practice, the Human Research Act and the Human Research Ordinance, as well as other locally relevant regulations. We have obtained ethical approval from the local ethical committee (Cantonal Research Ethics Commission on Human Beings, CER-VD, #2023-01846). After having received written information about the study, parents/guardians will give written informed consent for the participation of their child. The child will also give oral consent to participate in the study.

#### Ethical considerations

The main risk associated with filling out the questionnaires or tasks is that it may induce negative or uncomfortable thoughts or emotions. We will conduct a debriefing at the end of the assessments to discuss such issues and, if needed, refer the families to a mental health professional. Finally, at the participant’s request, the research team may provide oral, personalised feedback (general data and information regarding their participation).

#### Dissemination

We will follow open science transparency guidelines. Thus, we plan to preregister the main analyses before the end of data collection or, at the very least, before conducting the analyses. The results of the present study will be published in open-access, peer-reviewed academic journals. We will also organise symposia and poster presentations at key conferences in the field of child and adolescent mental health, as well as at meetings focusing on EMA. Additionally, findings will be disseminated to practitioners through the institutes’ close ties with other clinics and the educational sector. We further intend to make the main findings accessible to the general public in online and print magazines, at public events and on social media. A youth council will be involved in preparing the content and selecting the most effective media or way to reach the widest possible audience.

#### Scientific relevance

By using multimodal naturalistic methods with high ecological validity, the proposed project has the potential to add to the small evidence base of the distinction between tonic and phasic irritability in developmental psychopathology. In addition, the EMA allows for the investigation of within- and between-person variability in tonic and phasic irritability, and to explore their temporal sequences and direct precursors of the components of irritability as well as specify their natural context of expression. Moreover, using new multimodal technology to clinically characterise tonic and phasic irritability might inform the question whether tonic and phasic irritability are part of the same continuum or whether they represent two separate phenomena.^34^ Thus, this study will yield crucial data to develop new measures^13^ of tonic and phasic irritability.

In line with the most recent view of psychiatric disorders as continuous and dimensional phenomena rather than clearly delineated categorical entities, the proposed project thus takes a dimensional approach to quantification and severity of psychiatric symptomatology, abandoning the purely categorical diagnostic approach. Moreover, the naturalistic approach, including the parental perspective as well as using passive smartphone sensing, our project will lead to a better understanding of the contextual and interpersonal factors associated with irritability. Most importantly, our study is more likely to give insights into the psychophysiology of psychiatric disorders than approaches which examine disorders in a categorical manner.^123 124^ The proposed project, therefore, leverages the full spectrum of irritability in the help-seeking clinical sample and healthy control sample in combination with state-of-the-art clinical, cognitive, psychophysiological and neurobiological assessments, to contribute to the limited understanding of the underlying mechanisms of tonic and phasic irritability. Clinical re-evaluation of study participants will further allow us to determine the predictive value of tonic and phasic irritability for current and future psychopathology. The proposed project might further constitute the basis of a future cohort study. There is great potential in following these children up into adolescence and adulthood to understand the developmental pathways related to tonic and phasic irritability and its later consequences. A cohort study would further help to identify the best targets for early personalised intervention, reducing the negative long-term outcomes.

